### Trial design

The PIMS trial is a multicentre, parallel-group, superiority clinical trial with 1:1 randomisation. The trial will recruit 192 participants having surgery for large macular holes (≥400 μm), who will be randomly allocated into one of the two treatment arms:Face-down positioning: subjects will be advised to maintain a face-down position for a total of at least eight consecutive or nonconsecutive hours a day for 5 days following surgeryFace-forward positioning: subjects will be advised to maintain a face-forward position, inactive, for at least eight consecutive or nonconsecutive hours a day for 5 days following surgery

### Participants

The PIMS trial is being conducted at nine hospitals in the UK.

Patients are deemed eligible to participate in the study if they meet the following *inclusion criteria*:The presence of idiopathic full-thickness macular hole, ≥400 μm in diameter as measured by optical coherence tomography (OCT) scans, on either or both eyesPatients electing to have surgery for macular hole, with or without simultaneous phacoemulsification and intraocular lens implantAbility and willingness to position face-down or in an inactive face-forward positionPatients with a history of visual loss suggesting a macular hole of 12 months’ or less duration

Patients are deemed ineligible to participate in the study if they meet one or more of the following *exclusion criteria*:Age-related macular degeneration, glaucoma, diabetic retinopathy, retinal degeneration; amblyopia; previous vitrectomy surgery (refractive error, lens opacity, and previous use of ocriplasmin are not exclusion criteria)Traumatic macular holeHistory of visual loss suggesting macular hole duration longer than 12 monthsThe presence of retinal tear identified during surgery for which postoperative positioning is advised

## Outcome measures

The primary outcome of the study is the anatomical closure of the macular hole at 3 months post surgery.

Successful closure of the macular hole will be determined by OCT scans. The scans will be anonymised and sent to two independent retinal surgeons who will independently grade the macular hole as closed; ‘open and flat’ (without a cuff of subretinal fluid); or ‘open and elevated’ (with cuff of subretinal fluid). The readers will be masked to the identity and allocated treatment of the subject. In the event of any disparity in grading, a third independent retinal surgeon, also masked to identify and treatment allocation, will arbitrate.

The categories ‘open and flat’ (without a cuff of subretinal fluid), or ‘open and elevated’ (with a cuff of subretinal fluid) will be pooled into one category of ‘open’ for the purpose of analysis.

Secondary outcomes at 3 months post surgery are:Further surgery for macular holes, performed or planned (yes/no)Best-corrected visual acuity (BCVA) measured using a Snellen chart at a standard distance of 6 mPatient-reported experience of positioning on a scale from 0 (very difficult) to 10 (very easy)Patient-reported health and quality of life assessed using the National Eye Institute Visual Function Questionnaire (VFQ-25) from 0 (worst health and quality of life) to 100 (best health and quality of life)Patient-reported outcome ‘Given what you now know, would you still have elected to have the operation?’ with responses Yes, No or Don’t Know

## Sample size and randomisation

### Unit of analysis

All ocular assessments relate to the study eye. In the event that a subject is having surgery for bilateral macular holes (which are not operated on simultaneously), the first eye to be operated on during the trial will be the study eye.

### Sample size

Clinical consensus is that face-down positioning would be recommended if there were a difference of 15% in success rates. This is the smallest clinically relevant treatment difference that we wish to detect. Previous research [6] indicates that successful closure of large macular holes without advice to position face-down occurs in 80% of cases. A study with 86 patients per group has 85% power and 95% confidence to detect a difference in outcome rate of 80% in the face-forward positioning arm versus 95% in the face-down positioning arm. With an anticipated 10% loss to follow-up, we are aiming to recruit 96 patients in each arm.

### Screening

The PIMS trial did not collect data on the number of participants screened for eligibility. The reason for this omission is that the proportion of patients with macular holes ≥400 μm in size is a small minority of the overall number of patients presenting with macular holes. For some hospital sites, the data collection of the number of patients screened for eligibility was considered unfeasible given their current resources.

### Randomisation and masking

Patients are randomised in a 1:1 ratio to follow either a face-forward positioning or a face-down positioning. Randomisation is stratified by site, using random permuted blocks of size 4 or 6 in equal proportions. A secure bespoke online randomisation service implemented by the Pragmatic Clinical Trials Unit performs the randomisation. Randomisation is conducted post surgery to ensure masking the surgeon to the treatment allocated. Post surgery, trial staff input the patient’s ID and details for immediate on-screen randomisation. Randomisation is provided 7 days a week, 24 h a day. Each site is provided with a unique log-in username and password to access the service. Due to the open-label nature of the treatment, postoperative clinical staff and patients are unmasked to the treatment allocation.

Investigators assessing the primary endpoint by grading of the OCT scans are masked to the treatment allocation. In the event of any disagreement between the two clinician grades, a third independent retinal surgeon, who is also masked to the treatment allocation, will arbitrate.

## Analysis methods

### General analysis principles

The primary analysis for each outcome will be by intention-to-treat, meaning that all patients on whom an outcome is available will be included in the analysis, and will be analysed according to the treatment group to which they were randomised.

Through vigilance and careful planning, the PIMS trial management team aim to achieve complete capture of all data from all patients, including patients who do not adhere to the protocol or patients who withdrawal from the trial. We acknowledge that despite our best efforts, some patients may have missing data. In accordance with the intention-to-treat principle and to avoid concerns over data-driven selection methods, we state the plan for dealing with missing data here.

Missing data is a potential source of bias, and the extent and pattern of missing data can influence the interpretation of the trial. The sample size for the PIMS trial allows for a 10% loss of follow-up, and in our results we will provide a full listing of all the reasons for patients’ withdrawal of the study. This list will be helpful in justifying the assumptions that we make in regards to missing data; however, we cannot be certain that there is a relationship between observed covariates and missing outcome data, and cannot exclude the possibility of some data missing not at random.

We will analyse the data without undertaking any sensitivity analysis if the primary outcome is missing in fewer than 5% of cases (nine patients or less). If more than nine patients’ primary outcome is missing, we will undertake sensitivity analysis to test if the missing at random assumptions are appropriate. We will use a pattern-mixture approach to model the consequences of a systematic difference between missing and nonmissing values, to see if the conclusions drawn from the PIMS study are affected when the missing-at-random assumption is violated.

All analyses will be performed using Stata (Stata Corporation, College Station, TX, USA).

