### Variables measured and schedule of assessments

The variables measured preoperatively are age, sex, ethnicity, laterality, duration of symptoms, BCVA (Best-corrected Visual Acuity), lens status (either phakic or pseudophakic), macular hole diameter on OCT scans and the Quality of Life VFQ-25 questionnaireThe variables measured at 3 months postoperatively are BCVA, macular hole status (closed; open flat or open elevated), the Quality of Life VFQ-25 questionnaire, subject-reported experience of positioning and, if primary repair of a macular hole failed, was a second operation performed or planned?

For each comparison of outcomes according to positioning policy, the following summaries will be provided (see templates for tables in Additional file 1):The number of patients in each positioning policy group who are included in the analysisA summary measure of the outcome, by positioning policy group (mean and standard deviation (SD) for continuous outcomes, number and percentage in each category for categorical outcomes). The treatment effect (difference in means for continuous outcomes, odds ratio for binary outcomes) with its 95% confidence interval (95% CI) and *p* value

All comparisons will adjust for linear effect of macular hole size (μm) at baseline, phakic lens status at baseline, and a random effect of site (hospital). We will anonymise data reported by hospital site. Outcomes which are also assessed at baseline (BCVA and quality of life) will be analysed adjusting also for a linear effect of the baseline measurement.

Patients have a 2-week postoperative appointment, at which time clinicians may be able to identify that the macular hole closure was unsuccessful, meaning that a second operation to close the hole is required. The outcome of any participant who had a second surgery after randomisation but before the 3-month visit will be imputed as open, as it is most unlikely that the hole will close without further treatment by 3 months. These patients will not be completing secondary questionnaires.

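### Missing-data sensitivity analysis is triggered only by the count of missing primary outcomes, which does not register questionnaires left uncompleted after early re-operation

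*SAP article*

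**What the plan says.** All of this is in the SAP article.

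- **General analysis principles, analysis set.** The rule covers every outcome and uses available cases: "all patients on whom an outcome is available will be included in the analysis". The same section concedes that the authors "cannot exclude the possibility of some data missing not at random".
- **General analysis principles, switch.** Below the threshold: "We will analyse the data without undertaking any sensitivity analysis if the primary outcome is missing in fewer than 5% of cases" (nine patients or fewer). Above it: "If more than nine patients’ primary outcome is missing, we will undertake sensitivity analysis to test if the missing at random assumptions are appropriate". The method is a pattern-mixture model, used "to see if the conclusions drawn from the PIMS study are affected when the missing-at-random assumption is violated". No outcome is named for it.
- **Variables measured and schedule of assessments.** On early re-operation: "The outcome of any participant who had a second surgery after randomisation but before the 3-month visit will be imputed as open". On the same patients: "These patients will not be completing secondary questionnaires".
- **Analyses of secondary outcomes.** Regression models are specified for each secondary outcome. The one sensitivity analysis there re-pools observed don't-know answers. It does not deal with missing values.

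**The concern.** The section presents itself as the missing-data plan and opens with all outcomes in view, yet its only trigger reads one variable. That variable is a poor guide to how complete the patient-reported outcomes are, because of the plan's own handling of early re-operation. Such a patient adds nothing to the count of missing primary outcomes but is missing on every secondary questionnaire.

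This missingness follows from surgical failure, which the trial is designed to show differs between arms. It is therefore likely to be informative and unequal by arm. If patients with failed surgery would have reported worse scores, leaving them out removes poor scores mainly from the face-forward arm under the design assumptions. The available-case comparison could then be reported with an estimate and p value without any check on departures from missing at random, although the plan accepts that such departures are possible.

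**Working it through.** **Inputs.** From Trial design and Sample size: 192 patients allocated 1:1, 96 per arm; closure 80% face-forward and 95% face-down; 86 per arm before a 10% allowance for loss. From General analysis principles: the 5% threshold, given as nine patients. Not in the document: the share of failures re-operated before 3 months. I take this as an assumption and show 25% to 100%.

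**Step 1: reproduce the plan's figures.**
- Threshold: 0.05 × 192 = 9.6. Nine missing is 9/192 = 4.69% and ten is 10/192 = 5.21%, so nine or fewer is the correct count for below 5%.
- Sample size: two proportions, 0.80 against 0.95, two-sided 5% level, 85% power, no continuity correction, gives 86 per arm (power 85.1%). Then 86/0.90 = 95.6, rounded up to 96.

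Both agree with the SAP. The numbers are sound; the difficulty is which variable the threshold reads.

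**Step 2: expected failed closures at the design rates.**
- Face-forward: 96 × 0.20 = 19.2
- Face-down: 96 × 0.05 = 4.8
- Total: 24.0

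I use 96 per arm because the case of interest is the one in which no primary outcome is missing.

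**Step 3: questionnaires missing by design.** Missing = share re-operated early × expected failures.

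| Share re-operated before 3 months (assumed) | Face-forward | Face-down | Total of 192 | Primary outcomes counted missing |
|---|---|---|---|---|
| 25% | 4.8 (5%) | 1.2 (1.25%) | 6 (3.1%) | 0 |
| 50% | 9.6 (10%) | 2.4 (2.5%) | 12 (6.3%) | 0 |
| 75% | 14.4 (15%) | 3.6 (3.75%) | 18 (9.4%) | 0 |
| 100% | 19.2 (20%) | 4.8 (5%) | 24 (12.5%) | 0 |

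**Step 4: where the plan's own mark is passed.** Ten missing questionnaires need 10/24 = 42% of failures to be re-operated early. From there on the questionnaires exceed the plan's 5% while the trigger still reads zero. Ordinary non-return would add to these counts, but the document gives no rate for it and I have added none.

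**Step 5: which outcomes are affected.** VFQ-25, the positioning-experience score and the question on choosing surgery again come from patients, and the exclusion is worded for questionnaires. Further surgery is known for a re-operated patient. Whether visual acuity is measured in these patients at 3 months is not stated.

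**The case against.** The best reply is that the threshold sentence concerns missing primary-outcome data only. Read literally, its ban on any sensitivity analysis would also cancel the don't-know re-pooling, which has its own trigger, so the literal reading cannot be intended. On the narrower reading nothing is forbidden for secondary outcomes; the plan is merely silent, and many plans confine missing-data sensitivity work to the primary outcome. The SAP also allows for 10% loss, about 19 of 192, so on its own assumption the trigger may well be met. Numbers analysed by arm are already to be reported for each comparison, so a reader would see uneven missingness.

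Much of this is fair, and it limits the point in three ways.

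- A reader might infer that secondary outcomes never get a sensitivity analysis. The text does not support that. Above nine missing primary outcomes, the stated aim concerns the trial's conclusions in general and could be read to include them.
- A reader might infer that visual acuity has the same built-in gap. The exclusion names questionnaires only, so this is not shown.
- A reader might want the resulting bias in VFQ-25. The document gives neither the scores of the missing patients nor a standard deviation, and the planned analysis is on a logit scale with baseline adjustment. A shift in raw points would not answer the question.

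The reply does not remove the core. On either reading, with nine or fewer primary outcomes missing the plan provides no check for the questionnaires. Above nine, their own missingness still plays no part in the decision. Reporting the counts shows an imbalance but does not test what it does to the result. Nor is this only a matter of preference about scope, because the plan itself creates failure-related missingness in these outcomes and then measures completeness on a variable that does not register it.

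**Conclusion.** The point holds for the patient-reported outcomes when nine or fewer primary outcomes are missing. Above nine, coverage is ambiguous. At the design rates, 6 to 24 questionnaires would be missing with no primary outcome missing, in a ratio of four to one between face-forward and face-down. The plan's own nine-patient mark is passed once about 42% of failures are re-operated early. These figures assume that the design closure rates hold, that all 192 patients contribute a primary outcome, and that the early re-operation share lies between 25% and 100%; only the first comes from the SAP's design figures. The ratio follows from the 20% and 5% failure rates together with an equal re-operation share in both arms, and would change if either differed.

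The analysis of macular hole closure and the primary conclusion are unaffected. What is at stake is whether the secondary patient-reported results can be shown to be robust. The change is worth making, but the point does not threaten the trial's main result.

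**What to change.** Reword the threshold rule in General analysis principles so that it applies outcome by outcome:

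- For each primary and secondary outcome, count the missing values of that outcome. Count a questionnaire not completed because of re-operation as missing.
- Where the count exceeds 5%, run the planned pattern-mixture analysis for that outcome on its own analysis scale: log-odds for the binary outcomes, LogMAR for visual acuity, the logit-transformed score for VFQ-25. Allow the departure from missing at random to differ between arms.
- Remove the wording that lets the primary-outcome count decide for all analyses, and state whether visual acuity is recorded at 3 months in patients re-operated before then.

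This takes a few sentences in the SAP and a few extra sensitivity tables, using a method already specified. It needs no new data, visits or patients. The downside is slightly longer reporting and possibly more cautious wording where a secondary result proves fragile.

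### The SAP rules out any sensitivity analysis when nine or fewer primary outcomes are missing, yet that many can, if strongly unbalanced, change statistical significance (not direction)

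*SAP article*

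**What the plan says.** All of this is in the SAP article, mainly under General analysis principles.

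- The primary analysis uses observed outcomes only: "all patients on whom an outcome is available will be included in the analysis".
- The authors acknowledge that missing data can bias the result and that they "cannot exclude the possibility of some data missing not at random".
- The next paragraph sets a threshold. The data will be analysed "without undertaking any sensitivity analysis if the primary outcome is missing in fewer than 5% of cases (nine patients or less"). Above nine, where the "primary outcome is missing, we will undertake sensitivity analysis to test if the missing at random assumptions are appropriate", a pattern-mixture model is used.
- Under Variables measured and schedule of assessments, a participant re-operated before the 3-month visit is counted as open. The article gives no rule for other missing primary outcomes at or below nine.
- Under Sample size, the planned closure rates are "80% in the face-forward positioning arm versus 95% in the face-down positioning arm", and "With an anticipated 10% loss to follow-up, we are aiming to recruit 96 patients in each arm".

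**The concern.** The trial is decided by the number of open holes, which is small. A limit of 5% of all randomised patients sounds negligible, but nine unknown outcomes are not negligible beside the handful of failures expected in the better arm. The rule also considers only how many outcomes are missing. Nine missing from one arm are treated like a 5/4 split, although their scope to bias the comparison is quite different.

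Differential loss is conceivable here. The SAP describes face-down positioning as arduous, and patients and postoperative staff know the allocation. If the primary p value is near 0.05, or the missing outcomes fall mainly in one arm, the planned analyses would not show whether the finding depends on the unseen patients. A check added after unmasking would be post hoc.

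**Working it through.** **1. The plan's own figures.** Inputs from Sample size: closure 0.80 and 0.95, 85% power, 95% confidence (two-sided 5% inferred, because it reproduces the stated figure). Mean rate 0.875.

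n = [1.960·√(2·0.875·0.125) + 1.036·√(0.80·0.20 + 0.95·0.05)]² / 0.15² = 85.7, so 86 per arm. Then 86/0.90 = 95.6, so 96 per arm and 192 in all. Both agree with the SAP. The threshold also agrees: 0.05 × 192 = 9.6, 9/192 = 4.7%, 10/192 = 5.2%.

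**2. Expected events.** Open holes with 96 per arm: face-forward 0.20 × 96 = 19.2; face-down 0.05 × 96 = 4.8; total 24.

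**3. Method.** Two-sided pooled z-test (chi-square without correction) on open holes, face-forward v face-down. Each missing outcome is filled in as open or closed. This is unadjusted; the planned model adds hole size, lens status and site, so its p values would differ.

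**4. Planning rates, five missing face-down and four face-forward.** Observed 18/92 (0.1957) v 5/91 (0.0549). Pooled rate 23/183 = 0.1257; standard error √(0.1257·0.8743·(1/92 + 1/91)) = 0.0490; z = 0.1407/0.0490 = 2.87; p = 0.004. There are 6 × 5 = 30 completions. Three give p above 0.05:

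| Face-down missing open (of 5) | Face-forward missing open (of 4) | Completed table | p | Odds ratio for closure, face-down v face-forward |
|---|---|---|---|---|
| 4 | 0 | 18/96 v 9/96 | 0.062 | 2.23 |
| 5 | 1 | 19/96 v 10/96 | 0.070 | 2.12 |
| 5 | 0 | 18/96 v 10/96 | 0.10 | 1.98 |

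The 30 completions are not equally likely, so 3 of 30 is a count and not a probability.

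**5. All nine missing face-down.** 5% of 87 is 4.35, so both roundings are shown.

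- 19/96 v 5/87: p = 0.005. Four of nine open, 19/96 v 9/96: p = 0.041. Five of nine open, 19/96 v 10/96: p = 0.070.
- 19/96 v 4/87: p = 0.002. Six of nine open are needed to reach the same 19/96 v 10/96, p = 0.070.
- With all nine open the odds ratio is still above 1: 1.45 from the first table and 1.58 from the second.

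**6. The other way round.** 17/92 v 8/91: p = 0.056. If one of the four face-forward missing is open and the other eight missing are closed, 18/96 v 8/96: p = 0.035.

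**7. How often at the planning rates.** In 100,000 simulated trials (Wald test of the log odds ratio), the share of significant complete-case results that lose significance was:

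- 5/4 split, face-down missing all open and face-forward missing all closed: 54%
- all nine missing face-down and all open: 84% (direction changed in under 0.1%)
- 5/4 split, all nine open: 17%
- 5/4 split, each missing outcome open with probability one half: 11%

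**8. Does the cut-off separate safe from unsafe?** Ten missing, split 5/5, is 18/91 v 5/91. Its worst case is 18/96 v 10/96, p = 0.10, the same table as the worst case with nine missing in step 4. Only ten missing would trigger the check.

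**9. Chance that the exemption applies.** At the anticipated 10% loss, 192 × 0.10 = 19.2 missing. Treating losses as independent, P(9 or fewer | 192, 0.10) = 0.6%.

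**The case against.** The rule is fixed in advance, and the article gives avoiding data-driven choices as a reason. It leaves the primary estimate untouched. On the plan's own 10% loss the sensitivity analysis will almost certainly run. Counting re-operated patients as open removes an important informative route to missingness. The SAP also promises reasons for withdrawal, numbers analysed and outcome counts by arm, from which a reader could work out an unadjusted tipping point. At the planning rates with a near-even split, 27 of 30 completions stay significant. All of this stands, and it limits the point to a modest improvement.

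Three stronger readings are tempting, and the document does not support them:

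- **That nine missing outcomes could reverse the conclusion.** In every table above the odds ratio stays on the same side of 1. What changes is significance.
- **That nine is nearly twice the face-down failures.** 9/4.8 = 1.9, but this sets missing outcomes in both arms against failures in one. With a 5/4 split, four or five missing face-down compare with 4.8; against all expected failures the ratio is 9/24 = 0.38.
- **That the plan would present an unchecked result as robust.** The SAP says only that no sensitivity analysis will be done.

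What the objection does not answer is that failures lost without a recorded re-operation remain missing, and that the threshold takes no account of arm or event count.

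**Conclusion.** The concern holds in limited form. Having said that missingness not at random cannot be excluded, the SAP rules out the check for it at nine or fewer missing outcomes, using a cut-off unrelated to the number of events or the split between arms. Within that range significance can be lost from a planning-rate result (p = 0.004 to 0.062 or more in 3 of 30 completions; p = 0.005 to 0.070 with five of nine face-down missing open). It can also be gained from a borderline null (p = 0.056 to 0.035).

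Loss of significance at the planning rates needs strongly differential or otherwise extreme missingness. A result that starts nearer 0.05 needs less, as step 6 shows. The figures rest on the SAP's planning rates, except step 6, which is an illustrative borderline table; on 96 randomised per arm; and on unadjusted tests. The exemption matters only if loss falls below half of what was planned for.

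**What to change.** Delete the nine-patient threshold. Whenever any primary outcome is missing, run the pattern-mixture analysis that the SAP already names, allow the departure from missing at random to differ between arms, and report the tipping point. With nine or fewer missing, a small table of all completions is enough. Keep the re-operation rule and the primary analysis as they are.

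The cost is one deleted sentence, a little programming, and a few extra lines of reporting. No new data are needed. The article states that recruitment was still open at submission, so the change could be made before unmasking.
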